**Synopsis**

Sarcopenia is a progressive decline in skeletal muscle mass, strength and function with ageing, which puts older adults at increased risk of falls, frailty, disability, loss of independence and death. Sarcopenia is a major clinical problem that leads to increased use of health and social care. The loss of muscle mass and strength with ageing can be accelerated by other risk factors such as disease, physical inactivity, reduced mobility, and poor diet.

Adequate intake of dietary protein (amino acids, AA) in combination with resistance exercise (RE) are recognised as key modifiable factors in muscle ageing and physical decline. Intervention studies that investigated a combined effect of protein supplements (AA) and RE on muscle have observed that greater amounts of protein (~20g per meal) consumed repeatedly after exercise may result in increase in muscle mass in young and older adults. However, current research lacks in understanding the role of whole foods (e.g. milk and dairy products, fish, and meats) in attenuating the loss of muscle mass and function in older adults. Milk (cow) is a source of high quality protein (whey and caseins), minerals (calcium, phosphorus, magnesium), vitamins (A, D, E, B complex), and bioactive fats, and has many health benefits (e.g. reduced risk of diabetes, cardiovascular diseases, and obesity). Ratio of these nutrients, especially proteins and milk fat may be important for muscle health. Specifically, consumption of whole milk has been linked to reduced muscle soreness and damage after exercise, and better absorption of AA in the presence of milk fats and greater production of muscle proteins in young adults and athletes. Therefore, regular intake of high quality, nutrient-dense food such as whole milk in combination with RE may provide a platform for developing a strategy for maintenance of healthy muscles in older adults that does not involve drugs or medical products.

This pilot study will recruit 30 older adults aged 65 and over (≥65) who live in the community We will include individuals who have no known milk allergies and do not currently participate in structured gym program, and meet other inclusion and exclusion criteria as reviewed through their registering general practice within North East and North Cumbria Clinical Research Network, North East England. Eligible individuals will be randomly assigned to one of 3 groups: (group 1) ‘whole milk + RE’, (group 2) ‘skimmed milk + RE’, and (group 3) ‘control drink + RE’ (juice with added carbohydrates to adjust for energy in whole milk). Each 500ml of milk provides about 20g of protein. Participants in each group will receive a home visit from a trained researcher to complete sociodemographic and health questionnaire and functioning assessment over a period of 6 weeks (approximately). Next, they will complete a 6-week intervention (milk/ control drink + RE) twice a week at a sports/recreation centre under the supervision of an exercise physiologist. Right after exercise, participant will consume 500ml milk/ control drink within 40-45 minutes (supervised), and another 500ml at home over the next 4-5 hours (unsupervised). Another home visit will be conducted after the intervention is completed over a 3-4 week period (approximately), and will include similar health and functioning assessments from the first home visit, and will also gather participant views about participating in the study.

Study aims:

(i) Feasibility and acceptability of (whole) milk in combination with resistance exercise as an intervention to increase muscle function (physical performance), strength and mass in community-dwelling older adults aged ≥65 who may be at risk of sarcopenia. We will ask:

- Is an intervention of 2 × 500ml milk + RE twice a week for 6 weeks feasible?
- Is an intervention of 2 × 500ml milk + RE twice a week for 6 weeks acceptable to community-dwelling older adults?

(ii) To explore whether consumption of milk (whole and skimmed) in combination with RE has an influence on physical performance, muscle strength, muscle mass, self-reported quality of life, and activities of daily living in community-dwelling older adults who may be at risk of sarcopenia compared to control group (juice supplemented with carbohydrates + RE)?

(iii) To provide important information for planned future research.

# Background and rationale

#

The UK population is rapidly ageing; the number of adults aged ≥65 increased by 17.3% in the last decade, and in 2016 was estimated to account for 18% of the total population of 65.6 million^1^. The extraordinary gain in human longevity and the fast growth of the older population worldwide have been regarded as among the greatest accomplishments of humanity, but they are also a cause for concern and a societal challenge. The main challenge will be to maximise the potential for these extra years to be ‘healthy years’, and minimise burden from disease, disability, and dependency^2^. Genetic and non-genetic factors, such as smoking, physical activity and diet contribute to the heterogeneity in the ageing experience. There is a substantial evidence from experimental and observational studies to support the role of specific foods, dietary patterns, and nutrients in the prevention of chronic diseases and mortality^3^, and in improving the quality of life with ageing^4^. Understanding the important influences and mechanisms of healthy ageing such as diet and physical activity for optimising health and wellbeing in later life is essential for the development of effective interventions.

There is an increasing interest in understanding influences of sarcopenia, defined by both the European Working Group on Sarcopenia in Older People (EWGSOP) and a United States International Working Group as a progressive loss of skeletal muscle mass, strength and function with ageing^5^. Sarcopenia is strongly associated with adverse health outcomes in older adults, including frailty, falls, hospitalisation, disability and death^6^. The onset of sarcopenia is a central confounder for health of an older person, because skeletal muscle accounts for 40% total body mass, and serves as a vital protein store and metabolic regulator, in addition to its primary function related to posture, breathing, and mobility^7^. The prevalence of sarcopenia increases with advancing age, and reaches over 20% in very old adults (aged 85 and over)^8^. Costs associated with sarcopenia such as falls to the NHS are estimated to be more than £2.3 billion a year (NICE, 2013)^9^, emphasising the need for sustainable preventive measures aimed to preserve muscle health and function in a rapidly ageing population.

The loss of muscle mass and strength associated with ageing is further accelerated by acute and chronic stressors such as disease, physical inactivity, reduced mobility, and poor diet. Adequate intake of dietary protein (essential amino acids; EAA) from animal and plant sources in combination with resistance exercise (RE) are recognised as key modifiable factors in muscle ageing and physical decline^10,11^. Intervention studies that examined a combined effect of protein (EAA) supplements and RE to stimulate muscle protein synthesis (MPS) have observed an increase in total muscle protein by protein intake within 3-5 hours after exercise in both young and older adults^12^. Older adults experience a blunted response after protein ingestion to stimulate MPS, especially to lower amounts of protein (EAA) of <20g (<10g) compared with young adults. It has been shown that greater amounts of protein supplementation and periodic feeding in combination with repeated bouts of RE may results in increased muscle mass in older adults diagnosed with frailty and sarcopenia^13-15^.

However, current research lacks in understanding the role of whole foods (e.g. milk and dairy products, fish, and meats) in the prevention of sarcopenia in older adults, although the importance of a ‘whole food approach’ and the combined effects of nutrients within foods on health and functioning is well recognised^16^. Regular consumption of high quality, nutrient-dense foods, rich in macro- and micronutrients relevant for muscle health^17^ within a varied diet may provide a platform for developing strategies for maintenance of muscle strength, mass and function in older adults that do not include drugs, supplements and medical products.

Milk (cow) is an example of whole foods which may have potential to slow down and prevent muscle wasting. Whole milk is a source of high-quality proteins (6.3g/l (20%) of soluble whey proteins and 26g/l (80%) of insoluble caseins), minerals (e.g.1200 mg/l of calcium, 950 mg/l of phosphorus, 120 mg/l of magnesium), vitamins (fat-soluble A, D, and E and water-soluble B vitamins and vitamin C), bioactive lipids and fatty acids of which 30% are (mono and poly) unsaturated and 70% saturated fatty acids^18^. Whey protein supplements are considered superior to other protein sources to stimulate MPS after exercise in young and older adults^19^. Furthermore, intake of milk fats in whole milk increased the use of EAA for muscle protein synthesis after exercise in young men compared to fat-free milk^20^, suggesting additional benefits of milk lipids for muscle. Other benefits of milk (with milk fat) for muscle health include the reduction in exercise-related muscle damage, soreness, and decline in muscle performance in young adults^21^. Therefore, in addition to proteins, whole milk contains valuable minerals, vitamins, carbohydrates and milk fats (a delivery medium for fat-soluble vitamins A, D and E)^18^, and their ratio may be important for ageing muscle. Studies comparing the impact of low-fat versus whole milk providing >20g protein/day after exercise on muscle mass and function in older adults are lacking.

Milk and dairy product have other health benefits as an important part of a healthy diet across the life course, being crucial not only for the maintenance of bone density, but also associated with a reduced risk of adverse health outcomes, including diabetes, cardiovascular diseases, dementia, micronutrient deficiency, and obesity.

Taken together, whole milk (a functional food) in combination with RE could be beneficial for muscle health and function in older adults at risk of sarcopenia, and an important part of sarcopenia prevention in later life. Therefore, the main aim of this study is to explore the feasibility and acceptability of such an intervention in relation to physical performance, muscle strength and mass in community-dwelling older adults who may be at risk of sarcopenia.

This study is founded by the NIHR Newcastle Biomedical Research Centre, Newcastle University and Arla®, and sponsored by the Northumbria Healthcare NHS Foundation Trust, North Tyneside General Hospital (NTGH). The research team of the study has a combined expertise in geriatric^22,23^ and sports medicine^21^, gerontology^24,25^, nutritional interventions^21^ and population-based studies with older adults^24,25^. The host institutions (NIHR Newcastle Biomedical Research Centre and Institute of Neuroscience, Newcastle University) are recognised for their interdisciplinary research in ageing through translational pathway, and excellent collaborations on national and international scale.

**Hypotheses**

1. Consumption of whole milk (2 × 500ml; 2 × ~20g protein) after a RE session twice a week over the period of 6 weeks post-randomisation is feasible as an intervention in older adults (aged ≥65) who may be at risk of sarcopenia.
2. The intervention is acceptable with good compliance, low attrition, and no adverse health effects, including appetite suppression, negative dietary changes, muscle damage and soreness.

# Study aims

# Primary aims

1. Examine the feasibility and acceptability of (whole) milk in combination with RE as an intervention to increase muscle function (physical performance), strength and mass in community-dwelling older adults (aged ≥65) who may be at risk of sarcopenia through the following research questions:
2. Is an intervention of 2 × 500ml milk + RE twice a week for 6 weeks feasible?
3. Is an intervention of 2 × 500ml milk + RE twice a week for 6 weeks acceptable to community-dwelling older adults?
4. Provide essential data for planned future substantive research.

Secondary aim

1. Explore whether consumption of milk (whole and skimmed) in combination with RE has an influence on physical performance, muscle strength, muscle mass, and self-reported quality of life in community-dwelling older adults (aged ≥65) who may be at risk of sarcopenia.

# Primary and secondary outcomes of the study

Primary outcome measures

1. Feasibility and acceptability of the intervention (Time frame: 6 weeks post-randomisation and baseline assessment).
2. Measures to include: applicability, dosage and duration of the intervention, compliance, attrition, and adverse health effects such as appetite suppression, dietary changes and muscle soreness (Time frame: 6 weeks post-intervention).

Secondary outcome measures for exploratory analyses

1. Difference in physical performance measures: Short Physical Performance Battery^26^ (balance, 4m-gait speed, 5-chair stands) (Time frame: at baseline and after 6 weeks of intervention).
2. Difference in muscle strength measure: maximum strength test^27^ (grip strength, GS; Jamar hand-held 5030J1 dynamometer) (Time frame: at baseline and after 6 weeks of intervention).
3. Difference in muscle mass measure: Bioelectric Impedance Analysis (BIA; Tanita MC-780MA Body Composition Analyzer) (Time frame: at baseline and after 6 weeks of intervention)^28^.
4. Difference in self-reported quality of life measure: SF-12 (Time frame: at baseline and after 6 weeks of intervention)^29^.
5. Difference in activities of daily living measure: Barthel Index^30^.

# Study duration

The study will be conducted over 14 (maximum 15) months in total (01/05/2018 –19/08/2019). The end of the ‘active’ study period will be marked by randomisation of 30 eligible participants into the three intervention groups (i.e. (group 1) ‘whole milk + RE’; (group 2) ‘skimmed milk + RE’, and (group 3) ‘control drink’ + RE) and data collection from: (i) health and functioning assessments (baseline and post-intervention); (ii) nutrition + exercise intervention, and (iii) participants’ feedback about the study.

Although the end of the study is currently marked by the end date of funding (19/08/2019), we anticipate that this pilot study will lead to a main study funding application—as given within the main aims of the study.

# Inclusion criteria

1. Older adults aged ≥65 living in the community (not in care homes)
2. Registered patient with one of the General Practitioner (GP) surgeries within the NIHR North East and North Cumbria Clinical Research Network (CRN).

**Exclusion criteria**

1. Lacks capacity to consent—capacity is essential given the nature and demands of the research and the aim to gain participant feedback of the research experience
2. Self-reported lactose intolerance or milk allergies
3. Dislikes milk
4. Unable to understand instructions for muscle strength and function assessments in English or unwilling to participate in protocol when explained
5. Dislikes gym exercise with equipment
6. Doctor diagnosed diabetes I and II
7. Doctor diagnosed impaired renal function (estimated glomerular filtration rate <30ml/min/1.73m^2^)
8. Doctor diagnosed liver function impairment (e.g. viral hepatitis, alcoholic hepatitis, liver cirrhosis, biliary obstruction, non-alcoholic fatty liver disease, ischemic liver injury)
9. Significant respiratory disease (e.g. COPD, severe asthma, and bronchitis)
10. Doctor diagnosed gastrointestinal tract disease (e.g. gastritis, peptic ulceration, inflammatory bowel disease, gastric carcinoma, pancreas disease)
11. History of neuromuscular problems and all other co-morbidities that substantially interact with mobility and muscle metabolism (e.g. severe arthritis, rigidity, paralysis)
12. Pacemaker or severe heart failure or any other significant heart disease
13. Uncontrolled hypertension (160/100) and uncontrolled hypotension (<100 systolic)
14. Hip or knee replacement
15. An individual who the research team (i.e. exercise physiologist) evaluates as not suitable for the intervention because of safety reasons
16. BMI ≥30kg/m^2^
17. Unintentional weight loss ≥5kg for the last 3 months
18. Taking warfarin (because of possible interaction with control drink (cranberry juice))
19. Structured resistance exercise training and gym-based programme in last month
20. An individual who the General Practitioner feels it is inappropriate for the researchers to approach—the general practitioner has detailed knowledge of patients and may consider individual unsuitable for approach for reasons such as end stage terminal disease or safety risk such as any medical and physical conditions that preclude safe participation in an exercise programme.

Recruitment (main team member(s) responsible: [name])

Using inclusion/ exclusion criteria potential participants will be identified through multiple general practices in North East and North Cumbria CRN. Five recruitment sites were pre-screened for feasibility by North East and North Cumbria CRN (through local CRN support), and two GP practices in North Tyneside Clinical Commissioning Group (CCG) provided feedback during the application for the study funding.

Recruitment will be organised in two stages: pre-screening and screening. The pre-screening stage will first identify potential participants from participating general practices (GPs), who have agreed to review their patient database using predetermined exclusion/ inclusion criteria provided by the study team. For those GP patients who meet the criteria, surgeries will post recruitment packs on the behalf of the research team. Recruitment packs include: an invitation letter from the GPs, a Participant Information Sheet providing information about the study, a cover letter from the research group, a reply slip where individuals can indicate if they are interested in hearing more about the study, and a pre paid return envelope. The pre-screening stage then invloves a researcher telephoning those individuals who have expressed an interest in hearing more about the study via the reply slip and answering any questions they may have. With their permission the researcher will also conducting a 5-item SARC-F questionnaire^31^  to assess safety to proceed in the study and evaluate the use of SARC-F as a pre-screening tool for the inclusion of older adults in community-based studies involving resistance exercise program. The SARC-F questionnaire has five components (0-2 points for each) that assesses any difficulties with the following: (i) strength; (ii) assistance with walking; (iii) rise from a chair; (iv) climbing stairs, and (v) falls in the last year (Appendix 1).

Individual assessed to be unsafe to proceed will be informed in detail why they are not eligible for the study, thanked for their time and asked about the possibility to take part in other studies conducted by the AGE Research Group led by [name] [name].

Individuals assessed to be safe to proceed will be offered a home-based screening assessment, where possible this will be arranged at a day and time to suit potential particiapnts and their families if requested. This visit will be used to evaluate inclusion/ exclusion criteria not screened through general practices. The researcher will also measure participants’ grip strength and walking speed to evaluate their muscle strength and function based on the establish cut-offs (low grip strength: <20 kg in women, and <30 kg in men^5^; low walking speed: <0.8 m/s or ≥5 s over 4 m distance^5^). This information will serve two purposes: (i) for comparison with SARC-F results, and (ii) to allow equal distribution of those with some muscle strength weakness across intervention groups. For grip strength assessment, each participant will perform six trials (three in their right and three in their left hand, alternating between the hands), and the final grip strength value will be expressed as the maximum of the six trials. Each participant will complete walking speed assessment once.

The study aims to recruit 30 participants (15 men and 15 women) aged ≥65 years who meet the pre-screen and screening criteria. A reserve list of 6-9 eligible individuals will also be created to factor in replacement of those who withdraw early from the study.

**Randomisation** (main team member(s) responsible: [name])

Thirty participants will be allocated to one of the three intervention groups using a minimisation algorithm by an independent researcher. This will ensure the equal allocation of participants between the groups, so that gender and muscle strength (grip strength assessed at the screening assessment) are equally distributed and balanced between the groups. The researcher will use a free, open-source minimisation software (e.g. MiniPy 0.3, http://minimpy.sourceforge.net or OxMaR, www.ccmp.ox.ac.uk/oxmar), which features elements of randomness in the minimisation algorithm^32,33^. Briefly, the first subjects are allocated randomly into one of the interventions. Allocation of the subsequent participants will be based on hypothetical stepwise allocation of each individual to every group and computation of the imbalance score corresponding to each allocation. The imbalance scores will be compared and participants will be allocated to the group corresponding to the least imbalance score (preferred group). To ensure an element of randomisation, the participant is usually allocated to the preferred group with a higher probability (denoted as P_h_), and to other groups (non-preferred group) with lower probabilities (denoted as P_l_)^32,33^.

Because of the nature of the intervention, it is not possible to blind participants to intervention groups. The researcher team will not be blinded to nutritional part of the intervention.

Consent (main team member(s) responsible: [name])

Initial consent will be obtained by a researcher visiting the participants within their own home and conducting the screening assessment prior to randomisation to the study. The researcher will be suitably trained to conduct a 5-step informed consent process. The participants will be given enough time as needed to consent. The researcher must inform the participant that they are free to reconsider and withdraw from the study at any time. The notion of process consent will be implemented throughout the participants active research phase (i.e. from baseline to post-intervention assessment). Valid enduring consent will be assessed at the baseline assessment, intervention and post-intervention home visits. If a participant loses capacity to consent during the research process, he/she will be withdrawn from the study.

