**Data collection**

- HOME-BASED SCREENING ASSESSMENT (main team member(s) responsible: [name])

Researchers trained in assessment with older adults will visit potential participants selected through general practices and pre-screened with the SARC-F (i.e. evaluated by the research team as safe to proceed) in their own home to carry out screening for other exclusion/ inclusion criteria not assessed at pre-screening (e.g. milk allergies, participation in structured resistance exercise in the last month). Grip strength and walking speed will be measured to establish participants’ muscle strength and function status based on the established cut-offs^5^. An informed consent will be conducted before the assessments. Eligible individuals will be informed about the study procedure and their journey through the study (from randomisation to post-intervention assessment). Non-eligible individuals will be explained why they did not qualify for the study, thanked for their time, and will be informed about the possibility to participate in other studies led by [name] [name] (AGE Research Group).

This visit with the informed consent will last about 35 (maximum 40) minutes.

- HOME-BASED BASELINE ASSESSMENT: HEALTH AND FUNCTIONING PROFILE (main team member(s) responsible: [name])

Trained researchers will visit 30 participants enrolled in the study in their own home to conduct in depth interview and baseline assessments of the following domains:

1. Sociodemographic profile: age; sex; marital status; education; social class, and multiple index of deprivation
2. General health and functioning: SF-12 Health Survey^29^; self-reported diseases diagnosed by a doctor; list of medication (prescribed and over-the-counter); Mini Mental State Examination; Geriatric Depression Scale (15-item version) and Barthel Index^30^ (Activities of Daily Living); blood pressure (systolic and diastolic)
3. Dietary intake: 24-hr dietary recall (Intake24 (https://intake24.co.uk/) multi-pass, computerised 24-hr recall supported by the Newcastle University)
4. Appetite assessment: a 4-item Simplified Nutritional Appetite Questionnaire^34^
5. Self-reported physical activity: questionnaire assessing the frequency and duration of low intensity, moderate intensity and vigorous intensity physical activity, as assessed in the Newcastle 85+ study^35^
6. Anthropometry: demi-span (sex-specific height calculation), waist, hip and calf circumference

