Milk / control drink will be consumed as a bolus intake of 500ml under the supervision of a researcher immediately after exercise over 40-50 minutes during the recovery period (or longer if needed). Participants will be advised to resume their usual diet. Second dose of 500ml will be consumed at participants’ home over the next 4-5 hours. All drinks consumed at home will be clearly labelled as either ‘MIlkMAN study milk’ or ‘MIlkMAN study juice’. Second dose of 500ml can be consumed with other foods as a part of their usual diet (e.g. tea, cereal, mushed potatoes, etc.). Participants will be contacted by phone in the evening to check for muscle soreness and compliance with milk/ control drink consumption. Each participant will be provided with a plastic measuring jug (500ml) and a log sheet to measure and record milk/control drink consumption at home and to report it back to a researcher conducting the phone call.

On average, 500ml milk contains ~20g of protein needed to stimulate muscle protein synthesis above stimulation provided by RE. Whole (cow) milk (nutritional estimates of 22 UK samples during winter and summer) provides 66 kcal/100g of energy^44^. Fresh milk will be provided by Arla® (Nutrition Specialist: [name] at Arla Foods). Arla Cravendale® whole milk contains 3.6g fat, 3.4g protein, and 4.7g of carbohydrates per 100g of milk. Arla Cravendale® skimmed milk contains 0.3g fat, 3.6g protein, and 4.9g of carbohydrate per 100g of milk. Energy of control drink (cranberry juice; Ocean Spray Classic) will be balanced to match whole milk energy content and supplemented with maltodextrin (e.g. cranberry juice (45kcal/100g of energy^44^) will be supplemented with 6.05g of maltodextrin (3.8kcal/g) per 100g of juice; 1tsp = 15kcal; 30.25g for 500ml of juice).

Milk and control drink storage and handling

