There is also a small risk of gastrointestinal discomfort and possible unknown milk allergies (lactose or milk proteins). Participants who report any significant discomfort associated with milk or control drink intake (e.g. nausea, indigestion, diarrhoea, etc.) will be excluded from the study. In addition, there is a small risk of metabolic changes and weight gain due to the consumption of 650 kcal from whole milk and control drink (2 × week over 6 weeks) which will be counteracted by the increased energy expenditure during the RE programme. Appetite will be assessed at baseline and post-intervention, and total energy intake will be estimated using the Intake24 (computerised 24-hr dietary recall) pre- and post-intervention to examine any changes in energy intake. Also, weight and body fatness will be estimated using the Tanita Body Composition Analyzer at baseline and after the intervention.

There is also a small risk of falling during the walking test. However, the attending researcher will assess individual risk at the point of data collection (re-check exclusion criteria and endurance of consent) and omit measurements/ test if they felt it unsafe or that capacity to consent is not present or consent does not endure. It is made clear to participants that they are free to withdraw at any time. Should a decision to withdraw from the study be made, a reason for the withdrawal will be recorded. However, participants can withdraw without providing any explanation.

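### Dislike, allergy and intolerance are screened before randomisation for milk but not for the cranberry control drink, so compliance, attrition and tolerability do not start level across the arms

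*Protocol*

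**What the plan says.** Protocol, Exclusion criteria. Two criteria concern suitability for milk: "Self-reported lactose intolerance or milk allergies" (criterion 2) and "Dislikes milk" (criterion 3). One concerns the control drink, criterion 18: "Taking warfarin (because of possible interaction with control drink (cranberry juice". Criterion 4 is general and includes anyone "unwilling to participate in protocol when explained". No criterion names dislike, allergy or intolerance of cranberry juice or maltodextrin.

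Protocol, Data collection. The home screening visit covers criteria not yet checked, with the examples "e.g. milk allergies, participation in structured resistance exercise in the last month". Thirty participants are then split 10 to each arm. On the comparator: "Energy of control drink (cranberry juice; Ocean Spray Classic) will be balanced to match whole milk energy content and supplemented with maltodextrin". All arms take two 500 ml portions on each of two exercise days a week for 6 weeks.

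Protocol, Ethical considerations and risk and burden. "Participants who report any significant discomfort associated with milk or control drink intake" are to be taken out of the study. This rule operates after allocation.

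Protocol, Primary and secondary outcomes. Compliance, attrition and adverse health effects are among the primary measures. Data analysis and statistical methods calculates compliance for both milk and control drink. The intervention-versus-control differences it lists are physical performance, strength, muscle mass, quality of life and activities of daily living.

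**The concern.** With three-way allocation, each person randomised must be suitable for any of the three drinks. The protocol accepts this for milk, and for the juice as far as warfarin is concerned. It does not extend it to liking or tolerating the juice.

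Randomisation spreads dislike of juice evenly over the arms, but that dislike has an effect only where juice is drunk. Its milk counterpart would have acted in the other two arms and has largely been removed at entry. Participants know which drink they have, so preference can act directly on how much they consume and whether they continue.

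Three things are at stake:

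- Lower compliance or higher dropout in the control arm could be produced partly by the entry criteria and read as a property of milk.
- Each avoidable control withdrawal takes data from a comparator arm of only 10.
- A person with a known intolerance to the juice could be allocated to it without having been asked.

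**Working it through.** The protocol states no power calculation and no rate of drink dislike or intolerance, so there is no figure of its own to reproduce. The check has a textual part and an illustrative part.

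**1. Criteria set side by side**

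| Reason for unsuitability | Milk | Cranberry/maltodextrin drink |
|---|---|---|
| Allergy or intolerance | Criterion 2 | None |
| Dislike | Criterion 3 | None |
| Drug interaction | None | Criterion 18 (warfarin) |
| Unwilling once the protocol is explained | Criterion 4 | Criterion 4 |
| Significant discomfort after allocation | Removed from study | Removed from study |

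The last two rows are symmetric, and the drug-interaction row runs the other way. The gap lies in the first two rows.

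**2. Exposure in the control arm**

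From the Data collection section: 2 portions × 0.5 L × 2 days a week × 6 weeks = 12 L per participant. The arm has 10 participants (3 × 10 = 30).

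**3. Chance that the control arm contains affected people**

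Let d be the share of otherwise eligible people who dislike or cannot take the juice. This is an assumption, shown over a range. The expected number in the arm is 10d, and P(at least one) = 1 − (1 − d)^10.

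- d = 5%: expected 0.5; 1 − 0.95^10 = 0.40
- d = 10%: expected 1; 1 − 0.90^10 = 0.65
- d = 20%: expected 2; 1 − 0.80^10 = 0.89

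**4. What this could do to the primary measures**

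Compliance is consumption divided by expected consumption. Assume unaffected controls drink 95%. The fall in mean control-arm compliance is d × (95% − compliance of affected people).

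| d | Affected people drink 50% | Affected people drink none |
|---|---|---|
| 5% | 0.05 × 45 = 2.25 points | 0.05 × 95 = 4.75 points |
| 10% | 0.10 × 45 = 4.5 points | 0.10 × 95 = 9.5 points |
| 20% | 0.20 × 45 = 9.0 points | 0.20 × 95 = 19.0 points |

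For attrition, one withdrawal is 1/10 = 10 percentage points of the arm. That applies only to an affected person who actually withdraws, and the documents give no rate for this.

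**5. With symmetric screening**

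If the juice were screened as milk is, d in the control arm would fall to a small residual, comparable in kind to the residual left for milk. The differential shift would then be close to zero. No figure in the protocol changes.

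**The case against.** The case on the other side has real force.

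- A reader might infer that eligibility is screened for milk alone. Criterion 18 contradicts that, since it exists because of the juice.
- A reader might infer that a planned between-arm comparison of compliance or attrition is biased. The protocol states no such comparison. The hypotheses and primary aims ask whether milk with exercise is feasible and acceptable, and who dislikes juice does not alter that answer.
- A reader might infer that drink problems in the milk arms are zero by design. Criterion 2 relies on self-report, and the ethics section itself expects some unrecognised milk allergy and gastrointestinal discomfort. Disliking milk is also a coarser question than tolerating 500 ml of whole or skimmed milk twice in a day.
- The screening examples are not an exhaustive list. Candidates receive an information sheet, a telephone call and a consent visit, and criterion 4 removes those unwilling to follow the protocol.
- A reserve list of 6 to 9 people can replace early withdrawals, and poor compliance alone does not remove outcome data.

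All of this limits the point but does not remove it. Criterion 4 is not a dependable substitute: someone who dislikes juice has a two-in-three chance of milk and may reasonably agree to take part. The authors did not rely on criterion 4 for dislike of milk or of gym exercise, because they wrote separate criteria for both. The discomfort rule is even-handed, but it acts after allocation and so turns a juice intolerance that screening could have found into control-arm attrition. Replacement restores numbers but does not undo the recorded withdrawal.

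**Conclusion.** The asymmetry is real and can be read directly from the exclusion criteria. Dislike, allergy and intolerance are screened for milk, whereas the control drink is screened for warfarin use only. Compliance, attrition and tolerability are therefore not on an equal footing between the milk and control arms. Any reading of them across arms would tend to favour milk, and avoidable control losses would thin the comparator for the exploratory comparisons that are planned.

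The documents do not support calling this a demonstrated bias in a planned analysis. No contrast of these measures is specified, power is disclaimed, and the feasibility question for milk itself is untouched.

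The size is unknown. The 40% to 89% chance of at least one affected control rests on assumed rates of 5% to 20%, and it counts affected people rather than people who stop or drink less. This is an inexpensive improvement to a pilot, worth making before randomisation because it cannot be repaired afterwards.

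**What to change.** Replace criteria 2 and 3 with one criterion, applied at the home screening visit before randomisation: self-reported allergy or intolerance to, or dislike of, any study drink (whole milk, skimmed milk, or cranberry juice with maltodextrin). Keep criterion 18 unchanged. Record which drink led to each exclusion; this is also useful acceptability information for the main study.

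If allocation has already taken place, report compliance, attrition and tolerability within each arm, with drink-related reasons for withdrawal, and state that the entry criteria screened preference and tolerance for milk only.

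The cost is one amended criterion and one added screening question. The downside is a few more exclusions and a slightly more selected sample in all three arms. The recruitment cost should be small, given that the two practice database searches found on average 430 people per practice for 30 places. That count precedes the telephone and home screening stages.
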